### Outcomes

#### Primary outcome

The primary outcome is a change in mean SBP (mmHg) at month 6, which will be measured using a uniform Omron upper-arm electronic blood pressure monitor at each study site. The measurement will be performed when the patient is in a resting state.

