### Visit schedule

Patients will attend a baseline visit and 6 monthly follow-up visits. The follow-up visits will be scheduled every 30 ± 3 days. If a patient does not complete a follow-up visit within the scheduled period for any reason, we will not collect follow-up data for that time period, and the data for that visit will be considered missing. Patients who fail to attend three consecutive follow-up visits within the scheduled time frame will be excluded from the study. At the baseline visit, we will collect information about demographics, comorbidities, medication history, anthropometric measurements (blood pressure, heart rate, height, and weight), and QoL and hypertensive symptom scales. At each follow-up visit, we will record blood pressure, heart rate, new-onset disease or disease progression, treatment and expenses for the month, and AE data. As a basis for patient compliance judgment and subgroup analysis, we will also record the details of HSM, including the actual dosage, frequency, acupoints, and heat-sensitized sensations at each follow-up visit. QoL and hypertensive symptoms will be assessed at the 3- and 6-month follow-ups. The detailed visit schedule is presented in Fig. 2.

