### Statistical analysis

Data analysis of the primary outcome will be based on the full analysis set constructed by the intention-to-treat principle, whereby patients will remain in their original group regardless of contamination. The per-protocol set will also be analyzed by sensitivity analysis for the primary outcome to evaluate whether contamination impacts the direction of the effect. The secondary outcomes will also be compared based on the per-protocol set. The need to impute missing values will be determined by the proportion of and reasons for missing data. If imputation is necessary, appropriate methods, such as the last observation carried forward, “best-worst-case” scenario and multiple imputation regression modeling, will be chosen according to the distribution of the missing values.

Data analysis will be conducted separately for the randomized and nonrandomized groups, and consistency of effect directions between the two sets of analyses will be evaluated. For the randomized groups, repeated-measures analysis of variance will be employed for the continuous variables measured each month; QoL and symptom scale scores will be compared by *t* tests, and categorical variables will be compared by chi-square tests. These analyses will not be adjusted for covariates unless there are factors that are significantly unbalanced at baseline. For nonrandomized groups, we will utilize repeated-measures ANOVA, linear mixed models, and logistic regression models depending on the data distribution; potential confounders will be adjusted for, including age, body mass index (BMI), baseline SBP, duration of hypertension, type of antihypertensive regimen, diabetes, dyslipidemia, smoking, and alcohol consumption. The between-group difference will be measured by the mean differences for continuous outcomes (i.e., changes in SBP, DBP, dosage of antihypertensive drug, QoL, and hypertensive symptom scores) and the risk ratios (RRs) for binary outcomes (i.e., the response to treatment and incidence of new-onset cardiovascular events).

We are also interested in whether there are different blood pressure lowering effects between HSM regimens with different parameters, which will be explored by the following subgroup analyses with prespecified effect directions based on our clinical experience:

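### The missing-data method for month-6 SBP is to be chosen after the gaps are seen, from an open list that includes LOCF, which can bias the effect in either direction

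*Protocol article*

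**What the plan says.** All references are to the Protocol article.

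- **Primary outcome:** "The primary outcome is a change in mean SBP (mmHg) at month 6".
- **Statistical analysis, analysis set:** "Data analysis of the primary outcome will be based on the full analysis set constructed by the intention-to-treat principle".
- **Statistical analysis, model for the randomized groups:** "repeated-measures analysis of variance will be employed for the continuous variables measured each month". Linear mixed models are named only for the nonrandomized groups.
- **Statistical analysis, whether to impute:** "The need to impute missing values will be determined by the proportion of and reasons for missing data".
- **Statistical analysis, how to impute:** "If imputation is necessary, appropriate methods, such as the last observation carried forward", followed by best-worst-case and multiple imputation. The method "will be chosen according to the distribution of the missing values".
- **Visit schedule:** visits fall every 30 ± 3 days. For a visit not completed in that period, "we will not collect follow-up data for that time period, and the data for that visit will be considered missing". Patients who miss three visits in a row are excluded.
- **Sample size estimation:** 20% attrition is allowed for, with no split by arm.

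**The concern.** Two decisions about the primary comparison wait for the data: whether to impute, and by which method. The stated model makes these decisions hard to avoid. Classical repeated-measures ANOVA needs every visit, the visit rule turns late attendance into missing values, and the analysis set follows intention to treat. The trial must therefore either impute or lose patients from that set.

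The listed methods can give different answers, and LOCF suits this outcome poorly. The target is the month-6 value, and physicians may adjust drugs at each visit to bring pressure into range (Secondary outcomes). A pressure from an earlier month is thus a doubtful stand-in for month 6. At stake is the size of the primary effect and whether its confidence interval covers the truth at the nominal rate.

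**Working it through.** **1. The plan's own figure.** Inputs from Sample size estimation: difference 5 mmHg, SD 8 mmHg, two-sided alpha 0.05, power 80%, attrition 20%.

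N = 2 × ((1.960 + 0.842)/5)² × 8² = 40.19; 40.19/0.8 = 50.23, rounded up to 51 per group. The stated 51 reproduces. Nothing below changes the sample size.

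**2. How many patients have complete visits.** Assume 5% or 10% of visits are missed independently (not in the document). All six follow-ups are then present in 0.95⁶ = 74% or 0.90⁶ = 53% of patients. Classical ANOVA without imputation would use only these.

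**3. LOCF in closed form.** Assumptions not in the document: a proportion d drops out for good, the last attended visit is evenly spread over baseline and months 1 to 5, dropout is unrelated to outcome, and changes build linearly to month 6.

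- Mean fraction of the month-6 change that is carried forward: mean(0, 1, …, 5)/6 = 2.5/6 = 0.417.
- LOCF mean of an arm with true month-6 fall F: F × [(1 − d) + 0.417d].

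*Equal 20% dropout:* 5 × (0.8 + 0.2 × 0.417) = 4.42 mmHg. The corresponding values at 10% and 30% are 4.71 and 4.13. If the full effect is present from month 1, only patients last seen at baseline lose it: 5 × (1 − 0.2/6) = 4.83.

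*Unequal dropout with a common fall* (30% v 10% and falls of 5 or 10 mmHg are assumed). The factor is 0.825 at 30% dropout and 0.942 at 10%.

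| Dropout HSM / control | Common fall | HSM mean fall | Control mean fall | LOCF effect (true 5) |
|---|---|---|---|---|
| 30% / 10% | 5 | 10 × 0.825 = 8.25 | 5 × 0.942 = 4.71 | 3.54 |
| 30% / 10% | 10 | 15 × 0.825 = 12.38 | 10 × 0.942 = 9.42 | 2.96 |
| 10% / 30% | 5 | 10 × 0.942 = 9.42 | 5 × 0.825 = 4.13 | 5.29 |
| 10% / 30% | 10 | 15 × 0.942 = 14.13 | 10 × 0.825 = 8.25 | 5.88 |

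**4. Simulation.** Same dropout model, 80 per randomized group (60 compulsory plus 20 voluntary), SD 8, assumed correlation 0.6 between visits, 4000 runs, two-sample comparison of month-6 change.

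- Equal 20%, no common fall: LOCF 4.42 with 92.1% coverage of the true effect. Observed month-6 values give 5.00 with 94.7% coverage.
- 30% / 10%: 3.54 and 2.95, coverage 80% and 68%.
- 10% / 30%: 5.26 and 5.84, coverage 94% and 91%. These agree with the closed form within simulation error.
- No true effect: equal dropout gives no bias and type I error of 5% to 6%. Unequal dropout with the common falls gives a bias of about 0.6 or 1.2 mmHg and type I error of about 8% or 15%.
- The standard error from the LOCF analysis agreed closely with the spread of the LOCF estimates (1.25 v 1.25 at equal 20%).

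**5. Intermittent misses only.** If visits are missed independently with probability p, at the same rate in both arms, a missing month 6 is filled from about p/(1 − p) visits earlier on average. The shortfall is (5/6) × 0.053 = 0.04 mmHg at 5% and (5/6) × 0.111 = 0.09 mmHg at 10%.

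**6. Spread between listed methods.** Take 20% missing per arm and set best and worst values at 8 mmHg either side of the arm mean (assumption). The shift is 0.2 × 8 + 0.2 × 8 = 3.2 mmHg, so a 5 mmHg effect becomes 8.2 or 1.8. LOCF gives 4.4 under linear onset.

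**The case against.** Imputation is conditional, LOCF is one example among three, and being named first gives it no priority. Multiple imputation is on the same list. Data analysts will not know the allocation (Allocation), and the stated criteria are features of the missingness, not results by arm. An article also condenses the full plan, and thresholds or the order of sensitivity analyses commonly go in an SAP. Nor does the article say that incomplete patients are dropped from the ANOVA.

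Much of this stands. A reader might infer three stronger claims that the document does not support:

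- **That LOCF will be used and the result will be biased.** The text only allows it.
- **That LOCF understates its error.** Its standard error is right for the quantity it estimates. Coverage of the true month-6 effect falls because that quantity is not the true effect, and because the LOCF standard error is smaller than that from month-6 values actually observed (1.25 v 1.41).
- **That the bias works against HSM.** The Discussion warns about adherence to HSM, which is not loss to follow-up. HSM patients receive materials monthly, whereas control patients receive theirs only at the end (Recruitment and compliance enhancement), so retention could differ either way.

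Missed visits alone also cause almost no LOCF bias (step 5). The larger figures need permanent dropout.

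The objection does not remove the point. The absence of a threshold is not what is criticised. The article does state a data-dependent choice, calls LOCF appropriate, and names a model for the randomized groups that handles incomplete visits poorly. Blinding limits selective choice but does not correct LOCF bias.

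**Conclusion.** The point holds as a weakness in what the plan permits. The primary month-6 comparison has no fixed missing-data method, and one of the listed options can distort it.

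At the document's own 20% attrition, taken as equal by arm, LOCF would shrink a 5 mmHg effect to about 4.4 mmHg under linear onset, or about 4.8 if the effect is present from month 1. Errors above 1 mmHg appear only under assumed unequal dropout combined with a common fall in SBP: about 3.0 to 3.5 mmHg when HSM loses more patients. The reverse pattern inflates the effect to about 5.3 to 5.8 mmHg. Coverage is below 95% in all these unequal-dropout scenarios and at equal 20% dropout under linear onset. The direction cannot be known in advance, which is itself a reason to fix the method now. The onset shape, dropout timing, arm-specific dropout, common fall and correlation are all assumptions.

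**What to change.** In Statistical analysis, for the randomized groups:

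1. Replace repeated-measures ANOVA with a prespecified mixed model for repeated measures on all observed monthly visits. Make the month-6 treatment contrast primary, with no imputation. The model is valid if data are missing at random, and it keeps the observed visits of patients who later leave.
2. Remove LOCF from the list.
3. Use multiple imputation for the quality-of-life and symptom scales, which are measured at months 3 and 6.
4. Keep best-worst-case, or a delta-adjusted analysis, as a named sensitivity analysis for departures from missing at random.

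The cost is wording only, settled before analysis. Linear mixed models and multiple imputation already appear in the same section, and the sample size and visits stay as they are.

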**Discussion:**

This trial will provide important evidence regarding HSM as a technique for primary hypertension in primary healthcare settings. Given the randomization with patient preferences considered, the trial will also allow analyzing patient-preference effects and the comparison of randomized and nonrandomized samples, to improve the robustness and extrapolation of study conclusions.

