### Sample size estimation

The primary purpose of sample size estimation is to meet the need for statistical power for primary outcome comparison between randomized groups. Based on the results of our previous nonrandomized studies (not yet published) and expert opinion, we assume that the SBP in the HSM group will be on average 5 mmHg lower than that in the control group after 6 months of HSM treatment, with a common standard deviation of 8 mmHg between the groups. With a type I error probability “α” of 0.05 and type II error probability “β” of 0.20 and the allowance of a 20% attrition rate, a minimum of 51 patients in either the randomized HSM or control group is needed, as calculated by the following formula for the superiority design [22]:
$$ N=2\times {\left(\frac{Z_{1-\frac{\alpha }{2}}+{Z}_{1-\beta }}{\upmu_1-{\upmu}_2}\right)}^2\times {s}^2 $$

We ultimately decided to enlarge the total sample size to 400, as a sample of this size can be supported by funding. We administered a small preference survey to 100 patients at the study sites, which showed that the ratio of patients with a preference (a strong willingness to enter the HSM or control group) to those without a preference (accept the randomization) was approximately 6:1. Considering the feasibility of the study and the need for confounder adjustment, we established a sample size for the voluntary randomization group of 40 (20 per group) such that the size of the preference selection (nonrandomized) group would be 240 (120 per group). The remaining 120 patients will be entered into the compulsory randomization group (60 per group). Figure 1 illustrates the sample size scheme for each arm.

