## Discussion

Blinding is usually not feasible in RCTs involving healthcare techniques that require manual manipulation [23], including HSM. Consequently, patients will clearly know whether they are receiving the experimental intervention, and patient preference may cause uncertain effects on the study process and results [24, 25]. To reduce patient preference effects, we chose to perform a randomized patient preference trial, from which several advantages can be derived. First, this design allows us to analyze patient-preference effects by comparing the results of compulsory and voluntary randomization. Another benefit of a compulsory randomization group is avoiding being unable to achieve randomization when the proportion of patients who choose voluntary randomization is too small. Second, evaluation of randomized and nonrandomized samples will improve the reliability of the results if they can be corroborated. The evidence from nonrandom samples will also have better external validity. Third, this design will allow the study to recruit more participants, and the patients in the patient preference cluster will be more adherent to the protocol and less likely to be lost to follow-up.

A potential limitation of this study is that the patients in the HSM group may not easily adhere to the 6-month HSM treatment regimen, especially when the weather is hot. Although we will provide air-conditioned rooms at each study site for them to administer HSM, there is no guarantee that all patients will be willing to visit during the hot months of the summer. Nevertheless, patient compliance is an important outcome, and poor compliance would suggest that this community-based HSM model is not feasible. In addition, although the hypertensive symptom scale implemented in this study is from an authoritative guideline and has been used in a number of studies [15] to date, there is no direct evidence to support its reliability and validity.

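### Consistency between the randomized and nonrandomized results is judged by effect direction alone, which is too weak to support the reliability and robustness claimed from that comparison

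*Protocol article*

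**What the plan says.** In the protocol article, Statistical analysis: "Data analysis will be conducted separately for the randomized and nonrandomized groups", after which "consistency of effect directions between the two sets of analyses will be evaluated". By default the randomized analysis is unadjusted, unless a baseline factor is significantly unbalanced. The nonrandomized analysis is adjusted for a list of potential confounders. Between-group results are to be given as mean differences or risk ratios.

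Two other places attach weight to the comparison. The Discussion says that "evaluation of randomized and nonrandomized samples will improve the reliability of the results if they can be corroborated". The Discussion paragraph of the Abstract says that comparing the two samples serves "to improve the robustness and extrapolation of study conclusions".

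No criterion based on size, interval or interaction is given for this comparison. The subgroup analysis of compulsory against voluntary randomization lies wholly within the randomized patients, so it does not address it.

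**The concern.** The sign of an estimate discards how large the effect is and how well it is known. Two independent estimates can share a sign by chance, or because one or both are biased the same way, and they can share it while differing several-fold.

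Bias towards HSM is conceivable here. Patients and physicians are unblinded, a community physician at each site both trains patients in HSM and assesses outcomes, and the nonrandomized patients choose their treatment. Adjustment for the listed covariates does not cover motivation or expectation.

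At stake is how 240 of the 400 patients are used. If a matching sign is reported as corroboration, readers will take the nonrandomized arms to have confirmed the randomized effect, and to have supported its extrapolation, when the check could hardly have failed.

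**Working it through.** **Inputs** (Sample size estimation): "the SBP in the HSM group will be on average 5 mmHg lower than that in the control group"; "a common standard deviation of 8 mmHg between the groups"; "type I error probability “α” of 0.05" (two-sided in the formula shown); "type II error probability “β” of 0.20"; 20% attrition. Planned numbers per arm are 60 compulsory + 20 voluntary = 80 randomized, and 120 nonrandomized. After 20% attrition these are 64 and 96.

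**1. The plan's own figure.** N = 2 × ((1.96 + 0.842)/5)² × 8² = 40.19 per group; 40.19/0.8 = 50.23, so 51. This reproduces the stated minimum, so the inputs are read as intended.

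**2. Precision of each effect.** SE = 8 × √(2/n).
- Randomized, n = 64: 1.41 mmHg.
- Nonrandomized, n = 96: 1.15 mmHg.

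**3. Sign agreement.** Count a reduction in favour of HSM as positive. The two sets contain different patients, so the estimates are treated as independent. With p = Φ(true value/SE) for each set, P(agree) = p_R × p_N + (1 − p_R) × (1 − p_N).
- No effect in either set: 0.5 × 0.5 + 0.5 × 0.5 = 0.50, at any sample size.
- True effects 5 and 1 mmHg: p_R = Φ(3.54) = 0.9998, p_N = Φ(0.87) = 0.807; agreement 0.81.
- True effects 5 and 2 mmHg: p_N = Φ(1.73) = 0.958; agreement 0.96.

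**4. Residual bias.** The protocol gives no bias size, so the values b below are assumptions. HSM is taken to have no effect.
- The randomized estimate already favours HSM, with bias only in the nonrandomized arms: agreement is Φ(b/1.155). This gives 50% for b = 0, 81% for b = 1 and 96% for b = 2 mmHg towards HSM. For 1 mmHg the other way it falls to 19%.
- The same bias without conditioning on the randomized result: p_R = 0.5, so agreement = 0.5 × p_N + 0.5 × (1 − p_N) = 0.50 whatever b is.
- A bias shared by both sets, for example from open-label measurement: 55%, 66% and 89% for 0.5, 1 and 2 mmHg.

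**5. What the data could show instead.** SE of the difference between the two effects = √(1.414² + 1.155²) = 1.83; 95% half-width 1.96 × 1.826 = 3.6 mmHg. Without attrition (80 and 120 per arm) the SE is 1.63 and the half-width 3.2 mmHg. Against a randomized estimate of 5 mmHg, the difference (nonrandomized minus randomized) would read:

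| Nonrandomized estimate | Direction | Difference (95% CI) |
|---|---|---|
| 1 | agrees | −4 (−7.6 to −0.4) |
| 2 | agrees | −3 (−6.6 to 0.6) |
| 10 | agrees | 5 (1.4 to 8.6) |

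**6. An alternative criterion.** Suppose corroboration required the nonrandomized 95% CI to exclude zero in favour of HSM. With no true effect this happens with probability Φ(b/1.155 − 1.96): 2.5%, 14% and 41% for b = 0, 1 and 2 mmHg.

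**The case against.** The strongest reply is that the plan only says directional consistency will be evaluated. It sets no decision threshold, and the Discussion does not define corroboration as a sign match. Mean differences will be reported for both sets, so a reader would see 1 or 10 mmHg beside 5. The nonrandomized analysis is adjusted, the comparison is descriptive, and at the planned 5 mmHg effect in both sets agreement exceeds 99.9%. A condensed article may also leave interval reporting to a fuller document. All of this limits the consequence. It does not remove the point, because the article does name a criterion, names only that one, and claims reliability from the comparison. Near-certain agreement when HSM works is also of little use when agreement remains very likely with a much smaller nonrandomized effect.

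Four stronger readings are tempting and not supported:
- A reader might infer that slight confounding makes agreement more frequent in general. Step 4 shows otherwise. With no effect and bias confined to the nonrandomized arms, unconditional agreement stays at 50%. It rises only given a favourable randomized estimate with bias towards HSM, or with a shared bias.
- A reader might infer that corroboration is the stated reason for the 240 nonrandomized patients. Sample size estimation gives funding, the 6:1 preference survey, feasibility and confounder adjustment. The Discussion lists corroboration among several advantages.
- A reader might infer a risk to the primary conclusion. The comparison gates nothing, and the type I error of the randomized test is unchanged.
- A reader might infer that a nonrandomized interval excluding zero would settle the matter. That tests significance, not agreement. It would pass a precise 10 mmHg against 5, and 2 mmHg of pure confounding 41% of the time.

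**Conclusion.** The point stands as a weakness in a secondary, descriptive comparison. Direction is the only stated criterion, and it cannot support the reliability and robustness claims. Signs agree half the time when neither sample has an effect, and 81% or 96% of the time when true effects are 5 against 1 or 2 mmHg. Given a favourable randomized estimate and no true effect, 1 or 2 mmHg of bias towards HSM gives the same 81% or 96%.

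These figures assume SD 8 mmHg in both sets, 20% attrition, pooling of the compulsory and voluntary randomized arms, and independent estimates. The unequal true effects and the bias sizes are illustrative, since the documents give neither. Covariate adjustment would change the SEs somewhat. The 50% figure depends on neither the SD nor the sample size.

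**What to change.** In Statistical analysis, replace directional agreement with an estimate of the difference between the nonrandomized and randomized effects on month-6 SBP. Obtain it from a treatment by randomized/nonrandomized term with the same covariates in both samples, and report its 95% CI. This is an additional analysis; the primary randomized comparison stays as planned.

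In the Discussion and the Abstract, do not claim corroboration from direction alone. Limit the claim to what the interval supports, expected to be about ±3.6 mmHg (±3.2 without attrition). State that neither a matching sign nor a nonrandomized interval excluding zero rules out residual confounding. The difference estimate does not remove a bias common to both samples either, and this should be said too.

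The cost is wording and one extra adjusted model, including an adjusted randomized estimate, on data already to be collected. The downside is that the interval will be visibly wide.

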### Allocation

For randomization, the “blockrand” function in R 4.1.0 (Ross Ihaka, Robert Gentlemen, New Zealand) will be employed to generate random sequences. We will first divide the seven communities into the compulsory randomization cluster (three communities) and patient preference cluster (four communities) via cluster randomization. Then, we will generate a random sequence with a block size of four to randomly assign the patients into the HSM or control group in a 1:1 ratio in a compulsory or voluntary manner.

The random sequence will be concealed using scratch cards printed with a random number corresponding to the participation order. Until the coating is scratched, neither the patients nor the investigators will have knowledge about the group assignments. An independent investigator who is not involved in the implementation and follow-up of this study will generate and save the randomization sequence and prepare scratch cards. Although blinding is impossible for the patients and physicians, the data analysts will not be aware of the treatment allocation.

Patients who have a clear preference may be free to choose to enter the HSM or control group, with an allocation ratio of 1:1. Hence, when either nonrandomized group is full, the remaining patients will have to enter another nonrandomized group.

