#### Secondary outcomes

A change in mean DBP (mmHg) at month 6 as measured with SBP.The response to treatment at month 6, which is defined as an SBP reduction of ≥ 20 mmHg or DBP reduction of ≥ 10 mmHg for all patients, achieving SBP < 140 mmHg and DBP < 90 mmHg for patients ≥ 65 years or SBP < 130 mmHg and DBP < 80 mmHg for patients < 65 years [17].A change in the mean dosage of the original antihypertensive drug at month 6. At each visit, the physician will decide whether to adjust the original antihypertensive regimen administered to control blood pressure within the ideal range according to the blood pressure measurement, which will be recorded to assess this outcome.A change in mean QoL at month 6, as assessed by the Euro-QoL-5 Dimensions-5 Levels (EQ-5D-5L) questionnaire [19]. This questionnaire includes five items that evaluate QoL in terms of mobility, self-care, usual activities, pain/discomfort, and anxiety/depression. Each item receives a score from 1 to 5 (1, optimal QoL; 5, extremely poor QoL), and a comprehensive index value is calculated from these items, ranging from 0 (extremely poor QoL) to 1 (optimal QoL). The questionnaire also has an overall health status item assessed by a visual analog scale and scored between 0 and 100. A higher score indicates a better overall health status.A change in the mean severity of hypertensive symptoms scored by the symptom scale in the Guiding Principles of Clinical Research on New Drugs of Chinese Medicines at month 6 [20]. The scale assesses 24 hypertension-related symptoms. Each item receives a score of 0 to 3, and a higher score indicates higher severity of that symptom; the total score is the sum of the individual item scores and ranges from 0 to 72 (see details in Additional file 1).Incidence of new-onset cardiovascular events at month 6, including angina, myocardial infarction, and stroke. These data will be collected from patients and family self-reports.Patient compliance with HSM at each visit. This will be determined by the dosage of each administration and the weekly frequency of applications.Cost-effectiveness at month 6, as calculated by comparing the ratio of total treatment cost (China Yuan) to the rate of patients who achieve the targeted response to treatment between the HSM and control groups. Total and antihypertensive treatment costs will be analyzed. Outpatient and inpatient treatment frequencies and costs will also be compared.

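### Response to treatment in the randomised arms is tested by an unadjusted chi-square test, which is valid but probably gives up precision, by an amount that depends on a definition still to be made explicit

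*Protocol article*

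**What the plan says.** Protocol article, Secondary outcomes: the definition opens with "The response to treatment at month 6, which is defined as an SBP reduction of" at least 20 mmHg, or a DBP reduction of at least 10 mmHg, for everyone. After a comma it gives targets of below 140/90 mmHg from age 65 and below 130/80 mmHg under 65. No conjunction links the reduction to the target. The same section divides treatment cost by the rate of patients achieving the response to give the cost-effectiveness ratio.

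Protocol article, Statistical analysis: in the randomised arms "categorical variables will be compared by chi-square tests", and binary outcomes are summarised by risk ratios. Adjustment follows only if a factor is significantly unbalanced at baseline. The nonrandomised arms are adjusted for age, baseline SBP and other factors regardless. The economic evaluation is carried out only if the HSM group shows a better response.

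**The concern.** Age group fixes which target a patient must meet, and baseline pressure strongly affects whether it is met. Under Study population, ages 18 to 80 are admitted, so both targets apply. The 140/90 criterion there refers to diagnosis without medication and sets no floor at entry, so some treated patients may already be at target. Under Allocation, patients are put in blocks of four to "randomly assign the patients into the HSM or control group in a 1:1 ratio", with no stratification by age or pressure described.

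An unadjusted comparison leaves the variation explained by these factors in the error. The loss carries into the economic evaluation. The only route to adjustment is a significance test at baseline, which leaves the model open until the data are seen and can miss imbalances that matter. The planned consistency check would also set adjusted nonrandomised results beside unadjusted randomised ones.

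**Working it through.** **1. The plan's own figure.** Inputs from Sample size estimation: "With a type I error probability “α” of 0.05 and type II error probability “β” of 0.20"; "the SBP in the HSM group will be on average 5 mmHg lower than that in the control group"; "with a common standard deviation of 8 mmHg between the groups"; "the allowance of a 20% attrition rate".

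N = 2 × ((1.960 + 0.842)/5)² × 8² = 40.19 per arm; 40.19/0.80 = 50.23, rounded up to 51. The stated 51 reproduces. It concerns SBP only; nothing is stated for response.

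**2. Randomised patients.** 60 + 20 = 80 per arm; 80 × 0.80 = 64 completers per arm, 128 in all.

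**3. What the trigger would miss.** Assume a 5% two-sided test and 80 per arm.
- Half aged 65 or over (assumed): standard error √(2 × 0.5 × 0.5/80) = 0.079. Differences below 1.96 × 0.079 = 0.155, about 15 percentage points, go unadjusted.
- Baseline SBP SD 12 (assumed): standard error 12 × √(2/80) = 1.90. Differences below 1.96 × 1.90 = 3.7 mmHg go unadjusted, against a planned effect of 5 mmHg.

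**4. How predictable is response?** All inputs here are assumptions: baseline SBP mean 135/145/155 and SD 8/12/16, SD of change 8/12, 30% or 50% aged 65 or over, regression to the mean 0 or 0.3, DBP correlated with SBP. Share of control-arm response variance explained (median, range):

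| Reading | Age group + SBP | with DBP added |
|---|---|---|
| fall or target | 16% (1-40) | 20% (2-55) |
| target only | 29% (10-44) | 36% (11-60) |
| fall and target | 2% (0.4-5.5) | 3% (0.7-8) |

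Age group alone explains a median of 4% (fall or target) or 8% (target only).

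**5. Simulated comparison, 80 per arm.** 3,000 trials per row; mean SBP 145, half aged 65 or over, effects of 5 mmHg SBP (plan) and 3 mmHg DBP (assumed). Logistic regression on arm, age group and baseline SBP, standardised. Cells show the variance of the adjusted risk difference divided by that of the unadjusted one.

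| Baseline SD / change SD / regression to the mean | fall or target | target only | fall and target |
|---|---|---|---|
| 12 / 8 / 0 | 0.731 | 0.597 | 1.002 |
| 12 / 8 / 0.3 | 0.835 | 0.632 | 1.000 |
| 12 / 12 / 0.3 | 0.949 | 0.793 | 1.000 |
| 16 / 8 / 0 | 0.704 | 0.589 | 1.001 |
| 8 / 12 / 0.3 | 0.953 | 0.838 | 0.981 |

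The cut is therefore 5-30%, 16-41% and about 0-2%. For fall or target, power rises from 0.55 to 0.67 in the first row and from 0.49 to 0.52 in the third. For fall and target, the Wald test from the regression did worse than chi-square in the first row (0.20 against 0.37), a sign of sparse events.

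**6. Log risk ratio, 64 completers per arm, baseline DBP added.** Mean SBP 142, half aged 65 or over, 5 mmHg effect. Cut in variance:
- change SD 8, no regression to the mean: 36-44% (fall or target), 43-51% (target);
- change SD 8, baseline SD 15, regression 0.3: 27% and 37%;
- change SD 12, regression 0.3: 9-10% and 21-25%.

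Reading the plan's 8 mmHg as the SD of month-6 SBP, with an assumed correlation of 0.5 with baseline, gives 7-27% and 22-34%. A further set of runs at 64 per arm gives 11-41% and 24-48%. For fall and target, the runs show losses of about 1-13%; responders were 3-16% where recorded.

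**7. In patients.** Extra completers = 128 × (1/(1 - cut) - 1): 14 for a 10% cut, 32 for 20%, 85 for 40%, 128 for 50%.

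**The case against.** The strongest reply is that nothing here is wrong. A chi-square test between randomised arms is unbiased and controls type I error, the outcome is secondary, and no power is claimed for it. That stands: the point is efficiency. A reader might infer that the planned test is biased; the documents do not support that.

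A reader might also state as fact that 30-50% of the information is thrown away. The documents contain nothing from which a loss can be calculated. That range needs a wide baseline spread and a small SD of change. It is not clear that 8 mmHg is an SD of change: Sample size estimation attaches it to SBP after six months. A change SD of 8 with an independent baseline SD of 15 implies a month-6 SD of √(15² + 8²) = 17, about twice the stated figure. Drug adjustment at visits, described under Secondary outcomes, could weaken the link with baseline further.

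Nor do age and baseline pressure settle who responds. The reduction part is the same at all ages, and a higher baseline makes a large fall easier but the target harder, so the effects partly offset. Finally, the plan does provide for adjustment, though only after a significant imbalance. These replies limit the size of the point; they do not justify a data-driven trigger.

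**Conclusion.** The point holds as lost precision on a secondary outcome that gates and feeds the cost-effectiveness analysis. Under assumed inputs, prespecified adjustment for age group and baseline SBP and DBP would cut the variance of the log risk ratio by roughly 10-40% if response means a fall or the target, and by roughly 20-50% if it means the target. If both are required, there is no gain and possibly a small loss, because responders are few. The size rests on the assumed age mix, baseline spread, SD of change and regression to the mean, and first of all on how the two parts of the definition are joined, which the text leaves open.

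**What to change.** First, reconcile the wording under Secondary outcomes so that it states how the reduction and the target are joined.

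Then, unless both are required, replace the imbalance trigger for this outcome in the randomised arms with a prespecified regression of response on arm, age group (under 65, 65 or over), baseline SBP and baseline DBP. Standardise it to a marginal risk ratio with a confidence interval, keep the chi-square test as supportive, and use the adjusted response rates in the cost-effectiveness ratio.

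The Visit schedule already collects demographics and blood pressure at baseline, so no new data are needed. The cost is slightly more analysis work, and possibly some loss of precision if responders turn out to be very few.
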